**Table tab1:** 

Arms	Interventions
One functional fatty acids with a light fruity flavor	Dietary therapy method: Days 1–3: oral administration of functional fatty acids Days 4–6: oral administration of functional fatty acids
Placebo	Days 1–3: oral administration of placebo Days 4–6: oral administration of functional fatty acids

### Outcome measures

#### Primary outcome measures

The primary endpoint is the complete expulsion rate of small gallbladder stones at day 3 post-intervention, confirmed by two independent blinded ultrasound technologists. The complete expulsion rate at day 6 post-intervention is designated as a key secondary endpoint. Complete expulsion of small gallstones is defined as the absence of stone echoes in the gallbladder, with uniform anechoic patterns observed on ultrasound images. When stone echoes persist, multiple diameters of the stones will be measured via ultrasound to estimate their volume, which will then be compared with the preintervention volume to evaluate the partial expulsion amount and rate. The same method will be applied 6 days after intervention.

#### Standardized ultrasound assessment protocol

All ultrasound examinations will be performed using a Philips EPIQ 7 ultrasound system with a 3–5 MHz convex array probe, following a standardized protocol. Patients will be examined in the supine and left lateral decubitus positions after an 8-h fast.

*Image evaluation*: All images will be independently reviewed by two board-certified sonographers with ≥10 years of experience in abdominal ultrasound, who are blinded to group assignments and previous examination results.*Disagreement resolution*: Any discrepancies between the two reviewers will be resolved by a third senior sonographer, whose decision will be final.*Image storage*: Both static images (at least 2 images per examination, including longitudinal and transverse views of the gallbladder) and dynamic video clips (5–10 s per view) will be stored in a secure digital repository for future review and quality control.

Measurement standardization:

*Gallstone number*: Counted in multiple views to ensure all stones are identified*Maximum stone diameter*: Measured in three orthogonal planes, with the largest value recorded*Gallstone volume*: Calculated using the ellipsoid formula: Volume = (*π*/6) × length × width × depth*Gallbladder volume*: Calculated using the ellipsoid formula: Volume = 0.52 × length × width × depth*Gallbladder wall thickness*: Measured at the anterior wall of the gallbladder in the longitudinal view, avoiding the neck and fundus regions

#### Secondary outcome measures

Table 1 presents detailed information on the secondary outcome measurements. These data demonstrate the effectiveness and safety of the intervention process, as well as the potential risks.

**Table 1 tab2:** Secondary outcome measures.

Secondary outcome measure	Assessment time point	Operational definition
Gallbladder volume	7 days post-intervention	Measured by abdominal ultrasound using the ellipsoid formula: Volume = Length × Width × Depth × 0.52
Gallbladder wall thickness	7 days post-intervention	Measured by abdominal ultrasound at the thickest point, accurate to 0.1 mm
Serum total bilirubin	7 days post-intervention	Determined by standard laboratory assay; normal reference range: 3.4–17.1 μmol/L
Post-intervention abdominal pain	7 days post-intervention	Assessed using the Numerical Rating Scale (NRS)^1^; scores range from 0 (no pain) to 10 (worst imaginable pain)
Post-intervention acute pancreatitis	14 days post-intervention	Defined as the presence of characteristic abdominal pain plus serum amylase level ≥3 times the upper limit of normal^2^
Post-intervention gastrointestinal bleeding	14 days post-intervention	Defined as melena (black tarry stools) or a decrease in hemoglobin (Hb) level ≥20 g/L from baseline^3^
Post-intervention nausea, vomiting, and diarrhea	14 days post-intervention	Recorded as the daily frequency of each symptom during the 14-day follow-up period

^1^NRS: Numerical rating scale. A validated self-report pain assessment tool.

^2^Upper limit of normal for serum amylase at our institution: 100 U/L.

^3^Normal reference range for hemoglobin at our institution: 120–160 g/L (female), 130–175 g/L (male).

^4^All ultrasound examinations will be performed by two independent blinded sonographers with ≥10 years of experience in abdominal imaging. All laboratory tests will be conducted using standard methods at the Clinical Laboratory of the First Hospital of Lanzhou University.

Participant timeline please see Figure 2.

**Figure 2 fig2:**
[figure not shown]
Participant timeline: schedule of enrollment, interventions, and assessments^a^.

### Sample size calculation

In accordance with the ICH E9 Statistical Principles for Clinical Trials, this study is designed to scientifically evaluate the efficacy of functional fatty acids in the removal of small gallbladder stones while optimizing resource efficiency (minimizing cost) and study duration. The sample size calculation is based on rigorous statistical principles to ensure adequate power for detecting clinically meaningful treatment effects, with details as follows:

#### Primary outcome for sample size calculation

The primary outcome used to determine the sample size was the complete expulsion rate of small gallbladder stones at the end of the 6-day intervention period. Stone clearance is defined as the complete disappearance of sedimentary stones confirmed by abdominal ultrasound (the gold-standard imaging method for gallbladder stone assessment in this study), as assessed by two independent ultrasound technologists who are blinded to the treatment assignment. This outcome was selected because it directly reflects the core therapeutic goal of the intervention (i.e., removing small gallbladder stones) and is consistent with primary endpoints used in similar studies of gallbladder stone interventions (22).

#### Assumed outcome rates in the control and intervention groups

Three days after the intervention, the assumed clearance rate of small gallbladder stones in the control group (oral administration of a placebo for 3 days) was 8%. This estimate is supported by published literature on the natural history and placebo response of small gallbladder stones.

Three days after the intervention, the assumed clearance rate of small gallbladder stones in the experimental group (oral administration of functional fatty acids for 3 days, 50 mL/day) was 25%. This estimate is derived from a preliminary study conducted by our team from April to June 2024 (sample size = 20, approved by the Institutional Ethics Review Board: LDYYLL2023-529). In the preliminary study, among the 20 patients who received functional fatty acid treatment, 5 (25%) exhibited complete clearance of small gallbladder stones 3 days after the intervention. No serious adverse events were reported, and the compliance rate (≥80% of the planned dose) was 100%, confirming the feasibility of this intervention.

Therefore, we estimate that the assumed clearance rate of small gallbladder stones in the control group (3 days of placebo + 3 days of functional fatty acids) will still be 25% 6 days after the intervention. However, the assumed clearance rate of small gallbladder stones in the experimental group (oral administration of functional fatty acids for 6 days, 50 mL/day) will be greater than 25% 6 days after the intervention.

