**Methods:**

This prospective, single-center, double-blind, randomized controlled trial will enroll 100 adult patients with ultrasonographically confirmed small gallstones (maximum diameter <2 mm) and no prior treatment history. Participants will be randomly assigned at a 1:1 ratio to either the intervention group (*n* = 50), which will receive 50 mL of functional fatty acids daily on an empty stomach for 6 consecutive days, or the control group (*n* = 50), which will receive placebo for the first 3 days followed by the same dose of functional fatty acids for the subsequent 3 days. Abdominal ultrasound examinations will be performed on days 3 and 6 post-intervention to assess gallstone expulsion. Adverse events, including nausea, vomiting, abdominal pain, diarrhea, and signs of biliary obstruction, will be closely monitored throughout the study period.

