In our pilot study conducted from April to June 2024 (approved by the Ethics Committee of the First Hospital of Lanzhou University), we enrolled 20 patients with ultrasound-confirmed small gallstones (diameter <2 mm) who received 50 mL of functional fatty acids daily for 6 days. The results showed that 5 (25%) patients achieved complete gallstone expulsion at day 3, and 6 (30%) patients achieved complete expulsion at day 6. No serious adverse events were reported; only 2 patients experienced mild, self-limiting diarrhea that resolved without intervention. The compliance rate (defined as intake of ≥80% of the planned dose) was 100% (18).

Based on these pilot findings, we selected a 6-day intervention duration and established day 3 and day 6 as the primary observation time points, as most stone expulsion events occurred within this window. Additionally, the 25% complete expulsion rate at day 3 in the pilot study was used as the basis for our sample size calculation.

The underlying mechanism may involve greater gastrointestinal motility and increased secretion of cholecystokinin, which promotes gallbladder contraction and facilitates stone expulsion (12, 19–21). However, the limited sample size, absence of a control group, and uncertainty regarding the optimal dose and duration of treatment highlight the need for further investigations to validate these findings.

The aim of this study is to evaluate the efficacy of functional fatty acids as a noninvasive treatment for the expulsion of small gallstones. All participants will provide written informed consent prior to enrollment, and the study will be conducted in accordance with the Consolidated Standards of Reporting Trials (CONSORT) guidelines.

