### Aims and objectives

Our aim is to evaluate the efficacy and safety of oral functional fatty acids as a potential nonsurgical approach for promoting the expulsion of small gallstones.

Our specific primary objective is to compare the complete expulsion rate of small gallbladder stones at day 3 post-intervention between the two groups, as confirmed by two independent blinded ultrasound technologists. A key secondary objective is to compare the complete expulsion rate at day 6 post-intervention to evaluate the effect of treatment duration.

In addition, we will determine the incidence and severity of treatment-related adverse events (such as gastrointestinal symptoms and abdominal pain) in the treatment group according to the Common Terminology Criteria for Adverse Events (CTCAE) Version 5.0. In addition, we will evaluate the safety of the oral functional fatty acids by measuring changes in key biochemical markers before and after the intervention, including serum alanine transaminase (ALT), aspartate transaminase (AST), and total cholesterol. ALT and AST are sensitive markers of hepatocellular injury, and their measurement is necessary to assess whether oral administration of large volumes of fatty acids imposes excessive metabolic burden on the liver. Total cholesterol levels will be monitored to detect any adverse effects on lipid metabolism, as well as to evaluate potential changes in bile lipid composition that may contribute to gallstone formation or dissolution.

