The trial is being conducted at the First Hospital of Lanzhou University. The analysis will be based on intention-to-treat (ITT) and per-protocol (PP) methods. A minimum of 50 participants per group is needed to achieve 80% statistical power (with a two-sided *α* = 0.05) in detecting a clinically meaningful difference in the primary efficacy endpoint (e.g., the proportion of participants with complete gallstone expulsion within the treatment period). This sample size calculation is consistent with the superiority design, as it is powered to identify a significant between-group difference in favor of the experimental intervention.

Both participants and researchers will be blinded to the group assignments (double-blinding). The statistician conducting the analysis will remain unaware of the groupings, and the trial nurses will administer the oral treatment. Neither the participants nor the researchers will know which intervention each group receives. Unblinding will be permitted only at the time of statistical analysis, after the trial is completed. In case of an emergency (e.g., acute biliary obstruction), unblinding may be permitted to ensure participant safety. In such an event, the time, reason, and person responsible for the unblinding will be recorded promptly, and the trial monitor will be notified. Participants who are subject to unblinding will be excluded from the final efficacy analysis but will remain in the safety analysis.

In this study, gallstones with a diameter of less than 2 mm were selected as the target objects. The diameter of the cystic duct is generally approximately 2–3 mm, and the inner diameter of the common bile duct is 6–8 mm. Stones smaller than these ductal diameters have the anatomical feasibility to pass through. This selection not only allows the evaluation of gallstone expulsion in the early formation stage (where intervention may be most impactful) but also reduces the potential risk of biliary obstruction—an important safety consideration that aligns with the trial’s goal of assessing both efficacy (per superiority design) and safety.

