## Methods

### Primary objective

The primary aim of this study is to determine the effectiveness of oral functional fatty acids in facilitating the expulsion of small gallbladder stones. Upon trial conclusion and researcher and participant unblinding, the pre and postintervention ultrasound examination data will be meticulously analyzed to comprehensively compare the expulsion volume and expulsion rate of gallbladder stones between the experimental group and the control group on the third and sixth days after the intervention through in-depth intergroup comparisons. Moreover, we will perform a detailed analysis of the differences in the expulsion volume and expulsion rate of gallbladder stones within the experimental group to compare the outcomes after a six-day intervention with those after a three-day intervention; relevant data from the control group will be subjected to the same in-depth intergroup analysis.

We hypothesize that the stone expulsion rate among patients in the experimental group who will consume functional fatty acids for 3 days, will be significantly greater than that among patients in the control group who will take placebo over the same period. Additionally, we anticipate that the stone expulsion rate of the experimental group patients who will take functional fatty acids for 6 days will exceed that of the control group patients who will receive placebo supplemented with functional fatty acids. Furthermore, when the experimental group and the control group are compared, the volume of gallstones expelled and the expulsion rate following a six-day intervention are expected to be notably greater than those observed after a three-day intervention.

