### Statistical analysis

A predefined statistical analysis plan will be followed. All the statistical analyses will be conducted using IBM SPSS (Statistics 30.0.0). A *p* value of less than 0.05 will indicate statistical significance. Categorical variables will be reported as counts and percentages. Continuous variable data will be presented as mean ± standard deviation for normally distributed data, or median (interquartile range, IQR) for non-normally distributed data.

Analyses will be performed on both the intention-to-treat (ITT) population and the per-protocol (PP) population. The ITT population includes all randomized participants who received at least one dose of the intervention. The PP population includes only participants who completed the study protocol without major protocol violations.

The primary analysis will compare the complete expulsion rate of small gallbladder stones at day 3 post-intervention between the two groups using the chi-square test.

Key secondary analyses will include:

Comparison of complete expulsion rates at day 6 post-intervention between the two groupsWithin-group comparisons of changes in gallbladder volume and gallbladder wall thickness from baseline to day 3 and day 6Comparison of the incidence of adverse events between the two groups

For dichotomous variables, the chi-square test or Fisher’s exact test will be used as appropriate. For continuous variables, the independent samples t-test will be used for normally distributed data, and the Mann–Whitney U test will be used for non-normally distributed data.

After the last patient has completed the 30-day follow-up, a blinded endpoint adjudication committee will independently review all primary and secondary endpoint data.

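### The day-6 control rate of 25% does not carry forward the 8% assumed to clear on placebo, and no day-6 scenario built from the protocol's own figures reaches 80% power at 50 per arm

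*Protocol article*

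**What the plan says.** All references are to the protocol article.

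- *Assumed outcome rates in the control and intervention groups*: at day 3, "the assumed clearance rate of small gallbladder stones in the control group (oral administration of a placebo for 3 days) was 8" per cent, and the experimental rate is 25%, taken from the pilot (5 of 20). At day 6 the rate in "the control group (3 days of placebo + 3 days of functional fatty acids) will still be 25% 6 days after the intervention". The experimental rate at day 6 is described only as higher than 25%, without a number.
- *Background and rationale*: the only day-6 figure in the document comes from the single-arm pilot of 20 patients, where "6 (30%) patients achieved complete expulsion at day 6".
- *Primary outcome for sample size calculation*: the outcome used to set the sample size is complete expulsion at the end of the 6-day period.
- *Trial design*: day 6 is the second of two comparisons called primary. At least 50 per group is said to "achieve 80% statistical power (with a two-sided" α of 0.05), for an endpoint exemplified as complete expulsion within the treatment period.
- *Aims and objectives* and *Primary outcome measures*: day 3 is the primary endpoint and day 6 the key secondary. The key secondary objective is to "compare the complete expulsion rate at day 6 post-intervention to evaluate the effect of treatment duration".
- *Primary objective*: the expulsion rate in experimental patients treated "for 6 days will exceed that of the control group patients".

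**The concern.** The control arm's day-6 rate equals the 3-day active rate, as if nobody had cleared during the placebo phase, although the same section assumes that 8% do. A higher control rate shrinks the contrast on which the treatment-duration question rests. Because the experimental rate has no number, a reader cannot tell what day-6 difference is planned for or whether 50 per arm can detect it.

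At stake is the status of the day-6 result. The protocol treats it in places as primary and as the basis of the sample size, and predicts superiority. If its power is low, a non-significant result says little about duration, and the general statement of 80% power should not be read as covering it.

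**Working it through.** **Inputs.** Control day 3: 8%. Experimental day 3: 25%. Control day 6: 25% as stated. Pilot: 5/20 = 25% at day 3, 6/20 = 30% at day 6. Allocation: "randomly assigned at a 1:1 ratio", 50 per arm, or 45 after the anticipated 10% attrition (50 × 0.90). Test: chi-square, where a *p* "value of less than 0.05 will indicate statistical significance", two-sided.

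**The plan's own figure.** The base size of 47 per group cannot be reproduced. For 8% v 25%, two-sided α 0.05 and 80% power, the pooled formula gives (1.96 × √(2 × 0.165 × 0.835) + 0.842 × √(0.08 × 0.92 + 0.25 × 0.75))² / 0.17² ≈ 74 per group. Unpooled and arcsine versions give 71 and 70. No number at all follows from the day-6 assumptions, because one of the two rates is missing. The attrition step itself is in order: 47/0.90 = 52.2.

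**Step 1: day-6 control rate.**
- Placebo clearers all among those the oil would clear in 3 days: 8% + 17% = 25%.
- The 25% applies to the 92% not yet cleared: 0.08 + 0.92 × 0.25 = 31%.
- Fully additive: 8% + 25% = 33%.

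**Step 2: day-6 experimental rate.**
- Pilot: 30% (exact 95% CI about 12% to 54%). Only 1 of the 15 patients remaining after day 3 cleared on days 4 to 6 (6.7%).
- Optimistic assumption that 25% of the remainder clears again: 1 − 0.75² = 43.75%.

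**Step 3: power.** Exact enumeration of the two binomials under the Pearson chi-square test, counting only significant results that favour the experimental arm:

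| Experimental | Control | Difference (points) | 50 per arm | 45 per arm |
|---|---|---|---|---|
| 30% | 25% | +5 | 8.1% | 8.0% |
| 30% | 31% | −1 | 1.9% | 2.1% |
| 30% | 33% | −3 | 1.1% | 1.3% |
| 43.75% | 25% | +18.75 | 51% | 48% |
| 43.75% | 31% | +12.75 | 26% | 24% |

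Check of the first row by the normal formula: (0.05 − 1.96 × √(2 × 0.275 × 0.725/50)) / √(0.30 × 0.70/50 + 0.25 × 0.75/50) = (0.05 − 0.175)/0.0892 = −1.40, which gives 8.0%.

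**Step 4: what 80% power would need.** At 50 per arm the experimental rate would have to be about 52% against a 25% control rate, or about 59% against 31%. For 30% v 25%, 1,251 per arm would be needed.

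**Step 5: precision.** The 95% CI half-width for the day-6 difference is 1.96 × √(0.30 × 0.70/50 + 0.31 × 0.69/50) = 0.180, about 18 percentage points.

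**The case against.** **The 25% is not shown to be wrong.** This stands. The 31% needs placebo clearance to be unrelated to response to the oil, which the protocol does not state. If placebo clearers are a subset of oil clearers, 25% is coherent. The pilot's low clearance after day 3 points to patients differing in responsiveness, which makes that reading plausible. The fault is an unexplained value at the lower end of its range, not a proven miscalculation.

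**The 30% is a pilot result, not a planning assumption.** This also stands. The plan leaves the experimental rate open above 25%, and the pilot interval is wide; its upper limit of 54% just passes the 52% needed against a 25% control rate. A reader might infer that the plan itself predicts equal arms at day 6, or that the test cannot succeed. The documents do not support either. Pairing 31% with 30% also uses two different clearance rates for days 4 to 6 (25% in controls, 6.7% in the experimental arm), which agree only if the oil's effect is nearly spent after its first 3 days.

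**A secondary endpoint need not be powered.** This is true in general. It would answer the point if the protocol treated day 6 only as secondary, but *Primary outcome for sample size calculation* makes the 6-day rate the basis of the sample size and *Trial design* lists day 6 among the primary comparisons.

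**A null day-6 result need not be misread.** A reader might infer that it will be. *Trial design* explicitly says that day 6 compares two durations of active treatment, not active with placebo, and nothing in the document commits the investigators to a wrong reading. The risk remains because superiority is predicted without any statement of power.

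**Conclusion.** The concern holds in a limited form. The day-6 control rate of 25% omits the assumed 8% placebo clearance without explanation and is the lower end of a 25% to 33% range. The experimental rate has no number.

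At 50 per arm, the chance of a significant day-6 result favouring the experimental arm is about 1% to 8% with the pilot's 30%. With repeated 25% clearance it is 26% (control 31%) or 51% (control 25%), and lower still against 33%. The 51% is generous, because it lets clearance repeat independently in one arm while holding the other at the subset value. Omitting the 8% therefore matters most in the optimistic case, where it roughly doubles the apparent power.

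The conclusion that day 6 falls short of 80% does not depend on choosing 31% over 25%. It rests on the pilot's point estimate or the repeated-clearance assumption for the experimental arm; a true rate above about 52% would change it, but the protocol offers no such figure. The failure of 47 per group to follow from 8% v 25% is a separate fault. Correcting it to about 74 per group would still leave 25% v 30% far short of the 1,251 per arm required.

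**What to change.** - In *Assumed outcome rates in the control and intervention groups*: give the day-6 control rate as a range with its derivation (25% subset, 31% sequential, 33% additive). Give a numeric experimental rate or range (30% from the pilot to 43.75% if clearance repeats), and state the resulting power, about 1% to 51% at 50 per arm.
- In *Trial design* and *Primary outcome for sample size calculation*: state that the 80% power claim does not cover the day-6 comparison.
- In *Statistical analysis*: report the day-6 contrast as a risk difference with a 95% CI, noting the expected half-width of about 18 points. State that a non-significant day-6 result is not evidence that duration makes no difference, nor evidence against the day-3 result. The directional expectation in *Primary objective* may stay if it is marked as unpowered.

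The cost is wording only, with no added patients or procedures. The downside for the sponsor is a weaker claim about treatment duration.

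### The sample-size section names day-6 expulsion as the outcome that sized the trial, but the day-6 assumptions cannot yield a power figure and the stated 80% is unsupported there; day 3 should be the stated basis

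*Protocol article*

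**What the plan says.** All references are to the protocol article.

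- **Primary outcome for sample size calculation** gives the sizing outcome as the "complete expulsion rate of small gallbladder stones at the end of the 6-day intervention period".
- **Trial design** claims 80% power at two-sided 0.05 with at least 50 per group for the primary efficacy endpoint, which it illustrates as "the proportion of participants with complete gallstone expulsion within the treatment period". It also lists the day-6 contrast as the second of its two primary comparisons.
- **Primary outcome measures** makes day 3 primary: "The complete expulsion rate at day 6 post-intervention is designated as a key secondary endpoint". The Abstract and Statistical analysis agree. Background and rationale says the sample size rests on the pilot's day-3 rate of 25%.
- **Assumed outcome rates in the control and intervention groups** gives 8% (placebo) and 25% (active) at day 3. At day 6 the control rate "will still be 25% 6 days after the intervention"; the active rate is put above 25% without a number.
- **Background and rationale** has the only observed six-day figure: "6 (30%) patients achieved complete expulsion at day 6", out of 20.
- **Primary objective** predicts that the six-day arm's expulsion rate "will exceed that of the control group patients who will receive placebo supplemented with functional fatty acids".

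**The concern.** A power statement needs one outcome and two rates. The section that names the outcome points to day 6, where one of the two rates is missing. The sections that define the primary endpoint point to day 3, where both rates are given. A reader who takes the sample-size section at its word will credit the day-6 comparison with 80% power.

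That matters because Trial design uses the day-6 comparison to judge the effect of treatment duration, and Primary objective predicts superiority there. By day 6 both arms have had at least three days of active product, so the contrast is much smaller than at day 3. A non-significant day-6 result from a trial believed to have 80% power could easily be read as showing that three days are as good as six.

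**Working it through.** **Inputs.** Two-sided alpha 0.05, 80% power, 50 per group (Trial design; Allowance for participant attrition). Day 3: 8% vs 25%. Day 6: control 25%, active unquantified (Assumed outcome rates). Pilot at day 6: 6/20 = 30% (Background and rationale). Test: chi-square (Statistical analysis).

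**Step 1. The plan's own figure.** The plan's base size is 47 per group. For two proportions with mean p̄,

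n = [1.960·√(2p̄(1−p̄)) + 0.842·√(p₁(1−p₁) + p₂(1−p₂))]² / (p₂−p₁)²

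For 8% vs 25% (p̄ = 0.165) this gives 73.6, so 74 per group. Variants give 71 (unpooled variance), 70 (arcsine), 86 (continuity correction) and 58 (one-sided). None gives 47. At day 6 no n can be computed. Working backwards, 47 per group would need an active rate of about 53% against 25%, which the document nowhere assumes.

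**Step 2. Day-3 power at 50 per group.**

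power ≈ Φ{[(p₂−p₁) − 1.960·√(2p̄(1−p̄)/n)] / √([p₁(1−p₁) + p₂(1−p₂)]/n)}

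8% vs 25%: (0.17 − 1.960 × 0.0742)/0.0723 = 0.34, so 63%. Exact binomial enumeration of the uncorrected chi-square test gives 67%.

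**Step 3. Day-6 power at 50 per group, control 25%.** For 25% vs 30%: (0.05 − 1.960 × 0.0893)/0.0892 = −1.40, so 8.0%. Exact, both tails:

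| Active rate at day 6 | Exact power |
|---|---|
| 30% (pilot) | 8.7% |
| 35% | 19% |
| 40% | 36% |
| 45% | 56% |
| 50% | 75% |
| 52% | 81% |

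By the formula in Step 1, 25% vs 30% needs 1,251 per group for 80% power. The exact 95% CI for the pilot's 6/20 is 12% to 54%.

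**Step 4. The control rate at day 6.** Suppose 8% clear on placebo and stay clear, and three active days would clear 25% of all patients. The day-6 control rate then depends on the overlap:

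- full overlap (every placebo clearer would also clear on active): 25%
- independence: 1 − 0.92 × 0.75 = 31%
- no overlap: 8% + 25% = 33%

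The plan's 25% is the lowest of these. A higher control rate cuts power at a given active rate above it: at 40% active, power falls from 36% (control 25%) to 15% (control 31%).

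**Step 5. Precision at day 6.** With both rates near 30%, the 95% CI half-width is 1.96·√(2 × 0.3 × 0.7/50) = 0.18, or about ±18 percentage points.

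**The case against.** The strongest reply is that day 6 is a key secondary endpoint and need not have 80% power. Most of the text points to day 3: the Abstract, Primary outcome measures, Statistical analysis, the pilot basis in Background and rationale, and the only complete pair of rates. Trial design attaches the 80% to the primary efficacy endpoint and offers the treatment-period wording only as an example. On this view the sample-size section simply carries the wrong time point. This largely stands, and it shapes the repair. It does not remove the defect: the section as printed sizes the trial on day 6, and Trial design still ranks day 6 among its primary comparisons.

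Some stronger readings are tempting but not supported:

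- **That the true day-6 power is 5% to 9%.** The 30% is a 20-patient pilot result, not a design assumption. The 5% end sets 31% control against 30% active, which compounds two three-day periods in the control arm but not in the active arm. Compounding both gives 1 − 0.75² = 44% vs 31%, with exact power 26%. That is still low, but it is not 5%.
- **That day 6 must be non-significant whatever the product does.** A 52% active rate gives 81% power against 25%, and 52% lies inside the pilot's interval.
- **That 25% is an arithmetic error.** It is attainable under full overlap, and 31% needs independence, which the plan does not state.
- **That the hypothesis of results "following a six-day intervention are expected to be notably greater than those observed after a three-day intervention" must be deleted** because cumulative clearance can only rise. That sentence also covers stone volume, its contrast is unclear, and Statistical analysis lists no within-arm test of expulsion rate.

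Risk-difference reporting could also sit in an analysis plan that is not shown. That is fair. The statement of what the day-6 comparison can support belongs where the protocol makes its claim.

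**Conclusion.** The point holds as an inconsistency with a numerical consequence. The outcome named for sizing (day 6) conflicts with the primary endpoint and the stated sizing basis (day 3), and no day-6 power follows from the printed assumptions. With a 25% control rate and 50 per group, power is about 9% at the pilot's 30% and stays below 80% until the active rate nears 52%. A control rate of 31% to 33% would lower it further. These are scenarios, not the trial's known day-6 power. They rest on the plan's 25%, on no recurrence of stones, and on all 50 per group being analysed.

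Moving the basis to day 3 settles the conflict but does not restore 80%: 8% vs 25% gives 63% by formula and 67% exactly.

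**What to change.** 1. In Primary outcome for sample size calculation, name day-3 complete expulsion, in line with Background and rationale and Primary outcome measures. Restate the power of 50 per group there: about 63% to 67% for 8% vs 25%. Whether that power is acceptable is a separate decision for the sponsor.
2. In Trial design and Assumed outcome rates, state that the trial is not powered for the day-6 comparison. Give the day-6 active rate assumed, and present the control rate as an assumption with its range (25%; 31% under independence; 33% at most).
3. In Trial design and Primary objective, stop presenting day 6 as a primary comparison with expected superiority. Report it as a risk difference with 95% CI, note the expected width of about ±18 points, and say that a non-significant result does not show the two durations to be equivalent.

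The cost is wording only. The 80% statement is lost and one secondary claim is weakened. No visit, measurement or allocation changes.
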